### Sample Size

For this pilot study, the sample size was selected based on what the workplace deemed feasible (18 teams). With a usual team size of 10 to 15, and two-thirds expected to be eligible and participate (just over eight per team), we anticipate approximately 150 participants in total, with 75 randomized to each group. This sample size will provide adequate power (≥80% power) with 5% two-tailed significance, to detect short term (3 month) changes within groups (primary effectiveness aim) of our minimum difference of interest (MDI) in our primary outcomes of work and overall sitting time (see Table 2). All calculations are based on no multiple comparison adjustment to significance (in line with the exploratory nature of the study), an anticipated 30% attrition, and strong clustering (ICC=0.1) [58] with an anticipated design effect of 1.48 (ie, 1+0.1×4.83, with an average 5.83 participants per team). Under these same assumptions, power to detect changes equal to the MDIs for the secondary activity outcomes with 5% two-tailed significance are presented in Table 2 , along with the minimum detectable differences (MDDs) between groups for relative effectiveness (secondary aim). This pilot did not power a priori on other research questions, such as health outcomes and long-term changes (12 months). The MDIs and MDDs all reflected modest effects for activity. The assumptions regarding standard deviations (SD), pre-post correlations and clustering were informed by published and unpublished data from previous workplace interventions [38,58] and Australian population data from the AusDiab study.

**Table 2 table2:** Power to detect changes within groups (effectiveness) and minimum detectable differences between groups (relative effectiveness) with 5% significance, two-tailed.

Outcome	MDI^a^	Assumed values		Effectiveness	Relative effectiveness
		SD^b,c^	Pre-post *r* ^c^	Power	MDD^d^
Primary outcomes					
Work sitting time	45 minutes	90	0.6	90%	50 minutes
Overall sitting time	45 minutes	90	0.6	90%	50 minutes
Secondary outcomes					
Work prolonged sitting time	45 minutes	120	0.6	67%	65 minutes
Overall prolonged sitting time	45 minutes	120	0.6	67%	65 minutes
Work standing time	30 minutes	70	0.6	79%	35 minutes
Overall standing time	30 minutes	70	0.6	79%	35 minutes
Work stepping time	15 minutes	20	0.7	>99%	10 minutes
Overall stepping time	15 minutes	30	0.7	96%	15 minutes

^a^minimum difference of interest.

^b^standard deviation.

^c^assumed values based on unpublished data from the *Stand Up Victoria* trial

^d^minimum detectable difference with 80% power

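### Table 2 applies the design effect but not team-level degrees of freedom, so its figures are mildly optimistic; the standing MDD of 35 minutes falls short of its own 80% power definition

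*Protocol article*

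**What the plan says.** The Sample Size section of the protocol article says that "the sample size was selected based on what the workplace deemed feasible (18 teams") and that "we anticipate approximately 150 participants in total, with 75 randomized to each group". It allows for "an anticipated 30% attrition", an ICC of 0.1 and an average of 5.83 participants per team, which gives a design effect of 1.48. For within-group change in the two primary sitting outcomes it states: "This sample size will provide adequate power (≥80% power) with 5% two-tailed significance". It adds that "All calculations are based on no multiple comparison adjustment to significance".

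Table 2, titled "Power to detect changes within groups (effectiveness) and minimum detectable differences between groups (relative effectiveness) with 5% significance, two-tailed", then lists for each outcome the minimum difference of interest (MDI), the assumed SD and pre-post correlation, the within-group power, and the between-group MDD. Footnote d defines the MDD as the "minimum detectable difference with 80% power".

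The Design and Randomization sections make the work team the unit of clustering and of allocation. The Statistical Analyses section plans mixed models that allow for clustering, with adjustment for baseline in the between-group comparison.

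**The concern.** A design effect corrects the variance for clustering. It does not supply the degrees of freedom with which that variance is estimated. With about 9 teams per arm, the team-level information gives 8 df within one arm, or 18 − 2 = 16 when variance is pooled over both arms. A calculation that uses the df of the effective number of individuals sets the critical value too low and so reports too much power and too small an MDD.

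The standing MDD is a separate matter. The column is defined by 80% power, so every entry can be checked against that definition, and standing is the one outcome that falls short on the plan's own inputs.

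At stake is how the table is read later: whether a null between-group result is informative, and what a follow-on trial would assume.

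**Working it through.** **Inputs (Sample Size section and Table 2).** 75 per arm; 30% attrition; ICC 0.1; design effect 1 + 0.1 × 4.83 = 1.483; two-sided 5%. Teams per arm are derived: 52.5 / 5.83 = 9.

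**Effective n.** 75 × 0.7 = 52.5 completers per arm; 52.5 / 1.483 = 35.4.

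**Step 1: reproduce the stated powers.** SD of change = SD × √(2(1 − r)); noncentrality = MDI / (SD of change / √35.4).

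- Sitting: 90 × √0.8 = 80.5; 80.5 / √35.4 = 13.53; 45 / 13.53 = 3.33.
- Prolonged sitting: 107.3; noncentrality 2.49.
- Standing: 62.6; noncentrality 2.85.
- Overall stepping: 23.2; noncentrality 3.84.

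The noncentral t on about 34 df gives 89.8%, 67.9%, 79.1% and 96.2%, against the stated 90%, 67%, 79% and 96%. Work stepping exceeds 99% either way. Normal (z) critical values give 91.4%, 70.3%, 81.3% and 97.0%, a worse fit. The power column is therefore a t calculation with individual-level df.

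**Step 2: same noncentrality, team-level df.** The two-sided 5% critical value rises from 2.03 (34 df) to 2.12 (16 df) or 2.31 (8 df).

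| Outcome | Stated | 16 df | 8 df |
|---|---|---|---|
| Sitting (primary) | 90% | 88% | 83% |
| Prolonged sitting | 67% | 65% | 59% |
| Standing | 79% | 76% | 71% |
| Overall stepping | 96% | 95% | 92% |

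**Step 3: unequal team sizes.** The document gives no coefficient of variation (CV) of analysed team size, so it is an assumption here. Design effect = 1 + ((CV² + 1) × 5.83 − 1) × 0.1.

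| Assumed CV | Design effect | Sitting power, 16 df | Sitting power, 8 df |
|---|---|---|---|
| 0 | 1.483 | 88% | 83% |
| 0.3 | 1.536 | 87% | 82% |
| 0.4 | 1.577 | 86% | 81% |
| 0.5 | 1.629 | 85% | 79% |

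**Step 4: the MDD column.** With baseline adjustment the residual SD is SD × √(1 − r²), and the standard error of the difference is that value × √(2 / 35.4). For standing: 70 × √0.64 = 56; 56 × √(2 / 35.4) = 13.31; z-based MDD = (1.960 + 0.842) × 13.31 = 37.3.

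| Outcome | Stated MDD | z | t (about 69 df) | t (16 df) |
|---|---|---|---|---|
| Sitting | 50 | 47.9 | 48.6 | 51.1 |
| Prolonged sitting | 65 | 63.9 | 64.8 | 68.1 |
| Standing | 35 | 37.3 | 37.8 | 39.7 |
| Work stepping | 10 | 9.5 | 9.6 | 10.1 |
| Overall stepping | 15 | 14.3 | 14.5 | 15.2 |

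Standing is the only outcome whose printed MDD lies below the z and t values. Power at 35 minutes is 74.8% (z), 73.6% (t, about 69 df) or 69.5% (16 df). A change-score variance (41.7 by z) or a follow-up-only variance (46.6 by z) moves further from 35, so neither explains it.

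On 16 df the other printed MDDs also fall slightly below 80%: sitting 78%, prolonged sitting 76%, both stepping rows 79%.

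**The case against.** **Clustering is not ignored.** A reader might infer from an effective n of about 35 that the plan treats participants as independent. It does not: 35 is what remains after division by the design effect. Only the df refinement is missing, and on 16 df it costs 1 to 3 points of power. This stands.

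**The primary claim is not overturned.** A reader might conclude that the primary outcomes are underpowered. With equal team sizes, power is 83% even on 8 df. It drops below 80% only when 8 df is combined with an assumed CV of about 0.5. The document gives usual team sizes of 10 to 15 and no CV. It mentions small and large team strata at site A without giving a reason, so the strata are no evidence of marked imbalance. This also stands.

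**Type I error.** One might go on to argue that the analysis will exceed its 5% level. That would require large-sample tests, and the Statistical Analyses section names no reference distribution. The df method is commonly left to the analysis plan, so no such claim is made here.

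**Rounding.** All MDDs are multiples of 5, and rounding the z-based values to the nearest 5 yields every printed entry, including 37.3 to 35. That is a plausible explanation and suggests no deeper error. But the rounding is not stated, the power column fits t rather than z, the t value of 37.8 would round to 40, and 35 minutes still lacks the 80% power the footnote promises.

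**Little depends on it.** The size was set by feasibility in an exploratory pilot, the MDDs serve a secondary aim, and the table already shows powers below 80% for prolonged sitting and standing. This limits the severity but does not make the printed figures right.

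**Conclusion.** The point holds and is minor. Table 2's powers and MDDs are mildly optimistic because they use individual-level df with only 18 teams. Primary power is about 88% (16 df) to 83% (8 df) rather than 90%, so the claim of at least 80% remains sound for equal team sizes. The standing MDD of 35 minutes is inconsistent with footnote d in both rows: it carries about 74–75% power on the plan's inputs and about 70% on 16 df.

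These results rest on 9 teams per arm (derived from 18 teams and the 5.83 average), on the plan's ICC, SDs and correlations, on baseline adjustment for the MDDs, and on 8 to 16 df as the plausible range, since the exact df depend on the mixed-model method.

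**What to change.** - Restate the standing MDD in both rows as about 38 minutes by the plan's own approach, or about 40 on team-level df.
- Recompute the power column on team-level df and say whether 8 or 16 is used. Recompute the MDD column likewise; on 16 df the MDDs are 51 (sitting), 68 (prolonged sitting), 40 (standing), 10.1 (work stepping) and 15.2 (overall stepping) minutes.
- State any rounding, and round MDDs up so that each entry keeps the power that defines it.
- If a CV of team size is available, give it and carry it into the design effect.

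The cost is a revised table with slightly less favourable figures. The sample size and design stay as they are.

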### Statistical Analyses

Statistical analyses will be conducted in SPSS Statistics version ≥22 and Stata version ≥13 with statistical significance set at *P* <.05, two-tailed. Within-group changes in activity, work and health outcomes (continuous) will be assessed, using linear mixed-models that account for repeated measures and clustering, to determine the effectiveness of each intervention for these outcomes in the short- and long-term. To compare the relative effectiveness of the combined organizational-level and activity tracker intervention to organizational support alone, mixed-models will be used, adjusting for baseline values and potential confounders; these address both repeated measures and clustering. Confounders will initially be chosen a priori from the literature and retained in models if they are associated with the outcome at *P* <.2. Models will be checked for linearity, normality, and heteroscedasticity. Analyses will follow intention-to-treat principles. Per-protocol analyses will also be conducted to evaluate what the efficacy of the intervention is specifically for those who use the activity tracker, because activity tracker usage is self-directed. Assumptions regarding missing data will be checked and sensitivity analyses will be conducted to evaluate the impact of missing data on findings. Predictors of changes in activity will be evaluated by linear regression, adjusting for baseline values, and correcting for clustering. Predictors will be considered separately and also mutually adjusted. Characteristics of individuals will be considered as potential predictors including demographics (eg, age), psychosocial (eg, preference for sitting at work), health (eg, musculoskeletal problems) and work-related characteristics (eg, perception of relationship with supervisor), and engagement with the intervention (eg, LUMOback usage).

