### Randomization

Following manager consent, and prior to the information session, each team will be numbered randomly, using a random number generator, and then listed in numeric order. Teams will then be randomized to either Group 1 (organizational-level strategies only) or Group 2 (organizational-level strategies plus activity tracker), across location strata (site A and B) and team size strata within site A (small/large) using a randomization website [56]. The randomization schedule will be created by a university staff member not involved in the study. A project staff member will then apply the randomization schedule to the list of teams. Neither project staff nor participants will be blinded to participants’ randomization condition.

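### The randomised comparison screens its confounders on the outcome at P <.2 and does not commit to the randomisation strata as model terms; a fixed covariate set would be better (minor)

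*Protocol article*

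**What the plan says.** Randomization (protocol article): teams are allocated "across location strata (site A and B) and team size strata within site A (small/large"). That makes three strata: site B, site A small and site A large. Demographics and Job Characteristics says that project staff record team location and team size at baseline, so both are available for the analysis.

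Statistical Analyses: relative effectiveness is tested in mixed models that handle repeated measures and clustering, adjusted for baseline values and potential confounders, with "statistical significance set at *P* <.05, two-tailed". The baseline value enters without a screen. The rule for the rest is "Confounders will initially be chosen a priori from the literature and retained in models if they are associated with the outcome" at P <.2. Site and team size are neither listed nor excluded.

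Other Measures widens the pool of candidates. It puts individual, work, health and intervention factors forward as possible confounders for relative effectiveness.

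Aims and Sample Size class this comparison as secondary. Methodological Considerations says that each intervention's own effectiveness can be judged only as a single-group pre–post change, so Group 2 versus Group 1 is the only contrast that randomisation protects.

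**The concern.** The retention rule is stated text with two consequences.

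- **The model is settled by the outcome data.** A covariate unrelated to the outcome is kept about one time in five. The retained set can differ across the eight activity outcomes of Table 2, the health and work outcomes, and the 3- and 12-month assessments. Contrasts reported side by side may then be adjusted for different things.
- **The strata have no protected place.** They could enter only as confounders, and under the stated rule even listed strata would drop out whenever P ≥ .2. Stratified allocation balances the strata between groups. If they predict the outcome and are left out, the variation they explain stays in the error term, so the standard error is larger than the design warrants and the test is conservative.

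A related risk comes from Other Measures. Intervention factors can arise after randomisation, and a screen on association with the outcome would tend to keep them. Adjusting for them could remove part of the effect being estimated.

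**Working it through.** **Inputs from Sample Size and Table 2.** On the number of clusters, "the sample size was selected based on what the workplace deemed feasible (18 teams"). On size, "we anticipate approximately 150 participants in total, with 75 randomized to each group". The losses and clustering are "an anticipated 30% attrition, and strong clustering (ICC=0.1"), with an "anticipated design effect of 1.48 (ie, 1+0.1×4.83, with an average 5.83 participants per team"). The sitting row is "Work sitting time 45 minutes 90 0.6 90% 50 minutes": minimum difference of interest, SD, pre–post correlation, within-group power and between-group MDD. The MDD is at 80% power. Nine teams per group is assumed.

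**Step 1: reproduce the stated MDD.**
- Analysed per group: 75 × 0.7 = 52.5. Effective n: 52.5 / 1.483 = 35.4.
- Baseline-adjusted SD: 90 × √(1 − 0.6²) = 72.
- SE of the difference: 72 × √(2/35.4) = 17.1.
- MDD: 17.1 × (1.960 + 0.842) = 47.9 min (normal); 48.6 min (t on effective n); 17.1 × 2.985 = 51.1 min (t on 16 df from 18 teams).

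The stated 50 minutes lies between the two t versions, so the plan's figure is reproduced. The 16-df value is the reference below.

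**Step 2: force in the strata.** In units of the adjusted variance, a team mean has variance 0.1 + 0.9/5.83 = 0.254. If the strata explain a share R of the between-team part, this becomes 0.254 − 0.1R. Two stratum indicators leave 14 df, where the multiplier is 3.013. MDD = 3.013 × 72 × √((0.254 − 0.1R) × 2/9).

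| Assumed R | Variance of team mean | SE | MDD with strata (14 df) | Change from 51.1 |
|---|---|---|---|---|
| 0 | 0.254 | 17.1 | 51.6 | +0.5 |
| 25% | 0.229 | 16.3 | 49.0 | −2.1 |
| 50% | 0.204 | 15.3 | 46.2 | −4.9 |

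The documents give no value for R.

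**Step 3: how often would the stated screen keep the strata?** Assume three strata of six teams and a joint 2-df F test at P <.2. The noncentrality is 18 × 0.1R/(0.254 − 0.1R), which is 1.96 at R = 25% and 4.4 at R = 50%. The strata are kept about 45% and 68% of the time, and dropped about 55% and 32%. The gains in step 2 compare never adjusting with always adjusting, so they are upper bounds on what the stated plan loses.

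**Step 4: simulated behaviour** (18 teams, three strata of six, assumed covariates).
- Omitting the strata, against including them: at R = 30%, type I error 2.7% against 3.9% and power at 50 min 79% against 82%. At R = 60%, type I error 2.7% against 5.2% and power 79% against 87.5%.
- Screening four null team-level candidates without forcing the strata: power falls from 78–79% to about 71%. Forcing in all four falls further, to about 60%, when the strata do not matter.
- Screening eight individual-level candidates: SE 16.8–17.3 after the screen, against 17.4 with all forced in, so almost no precision is lost.
- Type I error under the screen stayed at or below about 5% throughout.

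**The case against.** The strongest reply is that the article condenses a fuller protocol, the analysis plan is not shown, and a full covariate list is commonly left to those documents. A reader might infer that the strata are left out of the analysis. The text does not support that: it never excludes them and it records both at baseline. This part of the reply stands. It does not reach the P <.2 rule, which is stated and which, applied as written, could remove strata that a fuller document had listed as confounders.

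A reader might also infer that every covariate is screened, or that the screen understates uncertainty. Neither holds. The baseline value, assumed to correlate 0.6–0.7 with follow-up, is always in the model. The other candidates are first drawn from the literature, so selection is not fully open. The simulations show no excess of false positives.

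The precision argument is conditional. With the baseline value already in the model, stable differences between sites or team sizes are partly absorbed, and R may be near zero. The screen also tends to keep strata that matter. Nor is adding terms free: with 18 teams, each team-level covariate costs degrees of freedom, and forcing in many does more harm than screening.

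Finally, the rule is attached to the relative-effectiveness model, so the primary within-group analyses are untouched. That stands and limits the weight of the point.

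**Conclusion.** The point holds in a limited form. In the trial's only randomised contrast, the covariates beyond the baseline value are chosen by their association with the outcome, the set may change with outcome and time point, and the stratification factors are not guaranteed a place. The main harm is loss of pre-specification, with a possible loss of power.

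Forcing in the strata changes an MDD of 51.1 min by between +0.5 min (R = 0) and about −2 to −5 min (R = 25–50%), and the gain over the stated screen is smaller. These figures rest on the plan's SD, correlation, ICC and attrition, on nine teams per group, and on shares of variance that are assumptions. Any error from omitting the strata is towards conservatism. Because the comparison is a secondary aim of an exploratory pilot, severity is minor.

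**What to change.** State one model for every outcome in the relative-effectiveness comparison:

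- Include group, time, the baseline value of the outcome and the three randomisation strata (site B; site A small; site A large).
- Add, if wanted, a short named list of covariates measured at baseline. Keep team-level additions to a minimum.
- Keep all terms regardless of their P values.
- Keep intervention factors that arise after randomisation out of this model; they belong in the predictor analyses.
- Confine the P <.2 screen to a sensitivity analysis.

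The cost is two degrees of freedom, about 0.5 min on the MDD if the strata turn out not to matter, and a change of analysis wording. No further data are needed.

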### Organizational-Level Intervention

All participants will receive the organizational-support intervention elements, which are based on the *Stand Up Australia* intervention [57]. The key intervention message is ‘Stand Up, Sit Less, Move More’ [57], which encourages staff to interrupt sitting at least every 30 minutes with a change in posture; replace sitting with standing or moving (working toward having equal amounts of sitting and upright activities in the day); increase physical activity of any intensity level; and to make these changes across the whole day, both during and outside of work hours.

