A LUMOback and a four-page instruction booklet that covers an introduction to the device, set-up instructions, and frequently asked questions will be distributed to Group 2 participants by the workplace champion following baseline assessments. On receipt of the device, participants will be asked to download the free app and sync the LUMOback with their phone. Participants will be asked to use their work email to set up their device as this will later be used to request the data from the company LUMO Bodytech. Participants can wear the device as much or as little as they like and their self-directed usage will be tracked. However, participants will be instructed by project staff to wear their LUMOback during the 3-month assessment period both to gather validity data and to estimate the intervention effectiveness while wearing the LUMOback. Participants will be allowed to keep the LUMOback.

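### The per-protocol analysis is said to give efficacy among tracker users, but use is self-selected after randomization, so its result could show a benefit from an inert tracker

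*Protocol article*

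**What the plan says.** Under Statistical Analyses, intention-to-treat governs: "Analyses will follow intention-to-treat principles". A second analysis is then added: "Per-protocol analyses will also be conducted to evaluate what the efficacy of the intervention is specifically for those who use the activity tracker". The reason given is "because activity tracker usage is self-directed".

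The Activity Tracker section confirms that use is a free choice: "Participants can wear the device as much or as little as they like and their self-directed usage will be tracked". There is one exception, at the primary time point: "participants will be instructed by project staff to wear their LUMOback during the 3-month assessment period".

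For the comparison of the two groups, "mixed-models will be used, adjusting for baseline values and potential confounders". The article does not say whether this adjustment carries over to the per-protocol analysis, nor what the users are compared with. The same section lists tracker usage among the candidate predictors of activity change.

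Both groups get the background program: "All participants will receive the organizational-support intervention elements". Methodological Considerations acknowledges that there is no untreated control, so each group's effectiveness is assessed pre–post only.

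**The concern.** The reason given for the analysis is also the reason it cannot deliver what it promises. Randomization makes the two groups comparable as allocated. It does not make people who choose to wear a device comparable with anyone else. If those inclined to wear it are also readier to sit less, the users-only result mixes that readiness with any effect of the device.

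The between-group comparison is planned with a minimum detectable difference of 50 minutes, larger than the 45-minute minimum difference of interest (MDI). A non-significant intention-to-treat comparison is therefore quite possible even with a modest true effect. A favorable result labelled as efficacy in users could then become the tracker finding that is carried forward, although the Conclusions offer the study as guidance for future interventions.

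**Working it through.** **Inputs from the protocol article (Sample Size and Table 2).** 75 per group, 18 teams, 30% attrition, ICC 0.1, 5.83 participants per team, SD 90 minutes, pre–post correlation 0.6, MDI 45 minutes, stated power 90%, stated minimum detectable difference (MDD) 50 minutes.

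**Step 1: reproduce the plan's own figures.**
- Design effect: 1 + 0.1 × 4.83 = 1.483. Effective n per group: 75 × 0.7 / 1.483 = 35.4.
- SD of change: 90 × √(2 × (1 − 0.6)) = 80.5 minutes. Power for a 45-minute within-group change: 89.8% (noncentral t) or 91.4% (normal approximation). Stated: 90%. It reproduces.
- Baseline-adjusted residual SD: 90 × √(1 − 0.6²) = 72 minutes. MDD: (1.96 + 0.84) × 72 × √(2 / 35.4) = 47.9 minutes. On change scores it is 53.6 minutes. The stated 50 lies between the two.

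The planning figures are sound, and 72 minutes is a fair residual SD for what follows.

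**Step 2: bias with a tracker effect of exactly zero.** Assumptions not in the document: users are the top share *u* of a normally distributed inclination to use; that inclination has correlation ρ with baseline-adjusted sitting reduction; users are compared with all of Group 1. Then

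bias = ρ × 72 × λ, with λ = φ(c)/u and c = z(1 − u).

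| Users in Group 2 | λ | ρ = −0.2 | ρ = 0 | ρ = 0.2 | ρ = 0.3 |
|---|---|---|---|---|---|
| 80% | 0.350 | −5.0 | 0 | 5.0 | 7.6 |
| 50% | 0.798 | −11.5 | 0 | 11.5 | 17.2 |
| 30% | 1.159 | −16.7 | 0 | 16.7 | 25.0 |

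Entries are apparent extra minutes of sitting reduction; negative values are apparent harm. Example: 0.3 × 72 × 0.798 = 17.2. For ρ of 0.2 to 0.3, the range runs from 5/45 = 11% to 25/45 = 56% of the MDI.

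**Step 3: chance of a falsely significant benefit (nominal 2.5%).** By normal approximation at 80%, 50% and 30% users it is 4.7%, 8.6% and 11.4% for ρ = 0.2, and 6.3%, 14.4% and 20.8% for ρ = 0.3. A simulation of 18 teams of 6 with ICC 0.1 (4000 runs per setting) gave biases of 11.6 and 17.0 minutes at 50% users and 17.3 and 25.1 at 30%. Its false-positive rates were 8.3% and 12.4% at 50% users, and 12.2% and 19.3% at 30%.

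**Step 4: the pre–post reading.** If the analysis is instead the users' own change from baseline, that change also holds the organizational strategies, which everyone receives, and any time trend. As an illustration, if those strategies alone moved sitting by the 45-minute MDI, users would show 45 minutes with an inert tracker, with no correlation between use and outcome needed.

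**Step 5: precision of a complier-average estimate.** With no use in Group 1, the standard error scales by 1/*u*: 1/0.8 = 1.25, 1/0.5 = 2, 1/0.3 = 3.3. The stated 50-minute MDD becomes about 62.5, 100 and 167 minutes.

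**The case against.** A reader might infer that the analysis would show a benefit even if the tracker did nothing. The documents do not support that. For the comparison with Group 1 it needs a positive residual correlation between use and sitting reduction, and none is given. At zero correlation there is no bias, and at a negative one the tracker looks harmful. Even at ρ = 0.3 with 30% users, a falsely significant benefit arises in only about one trial in five.

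Other points stand in part:
- **Comparator.** The per-protocol sentence names none; all of Group 1 is an inference. The comparator and the definition of a user may sit in a fuller document, so their absence is not counted here.
- **User share.** Participants are told to wear the device during the 3-month assessment. If use is defined then, the share may be high and the bias near the 5–8 minute end. Those who comply may still differ from those who do not.
- **Adjustment.** Other Measures collects technology confidence, use of other devices and preference for sitting or standing as potential confounders. Adjusting for them could shrink ρ. However, they are retained by association with the outcome, not with use, and measured factors need not capture readiness to change.
- **Weight.** The analysis is additional to intention-to-treat, the tracker comparison is a secondary aim, and the study is an exploratory pilot.

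A reader might also infer that an instrumental-variable analysis should simply replace the per-protocol one. That goes too far. Individuals consent after their team is allocated, and tracker teams receive device details at recruitment, so enrolment may differ by group. Methodological Considerations anticipates Group 1 responding to visible cues from wearers. With 18 teams the interval would be wide.

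None of this rescues the word efficacy for a self-selected subgroup.

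**Conclusion.** The concern holds as a wrong claim about a stated analysis. Neither users against Group 1 nor the users' own pre–post change estimates efficacy in users, and either could favor an inert tracker. For the first reading, with assumed correlations of 0.2 to 0.3, the spurious reduction is about 5–8 minutes at 80% users, 11–17 at 50% and 17–25 at 30%. These figures rest on the inferred Group 1 comparator, a normally distributed inclination to use, and baseline adjustment only. They show what is possible and are not a prediction, since the protocol fixes neither the user share nor the correlation. The governing intention-to-treat analysis and the primary within-group aim are not affected by this point.

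**What to change.** 1. Describe the users-only result as exploratory and associational, and drop the word efficacy for it.
2. State that conclusions about the tracker rest on the randomized intention-to-treat comparison.
3. If an effect in users is wanted, add a complier-average estimate: randomized group as the instrument for use, baseline-adjusted, with team-clustered errors and a use threshold fixed from device data before outcomes are analyzed. Any Group 1 use can be taken from the questionnaire.
4. State the limits of that estimate: a standard error about twice as large at 50% use and about three times at 30%; the assumption that an unused tracker, or wear below the threshold, has no effect; possible spillover to Group 1; and consent after allocation, which bears on the intention-to-treat comparison too.

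The cost is wording and a modest amount of analysis. Data collection has finished with results pending, and usage data were already planned, so nothing new needs to be collected.
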